### Sample size

The Cobb angle at inclusion will on average be 29 degrees (range 22–35 degrees). Due to the standard error of radiographic production and intra and inter-observer measurement variation, a measurement error in Cobb angles of 5 degrees will appear [1]. To reduce the standard error of radiographic production, all patients will undergo X-ray following a strict protocol. Because inter-observer measurements errors are reduced (see *Outcomes*), measurement error will than be maximal 2 degrees, thus the 95% observation interval of Cobb angles at inclusion is 20–37 degrees. After two years, when the outcome will be determined, the range in change will be 0–15 ± 2 degrees. Assuming a uniform distribution of this change in Cobb angle between the patients after two years (most unfavorable scenario), the standard deviation of the difference in change between baseline and outcome measurement will be about 4.5 degrees.

Since bracing has to be better than observation to be justified as treatment for IS, a superiority design will be used. With a power of 95% and alpha = 0.05, a mean difference of 5 degrees between the groups can be detected with 40 patients in both study arms. We will aim at a study population at start of 100 patients to take loss to follow-up into account.

### Randomization

Patients and their parent(s) who decide to participate will be asked to return the informed consent form to the researchers. Upon receipt of this form, randomization will be performed centrally by the department of Public Health (Erasmus MC) using computer-generated lists. Lists will be constructed with randomly permuted blocks per stratum, where strata will be defined by the participating center. The orthopedic surgeon will notify the patients and their parents of the outcome of allocation to the intervention group or the control group.

### Blinding

In this study, blinding of patients and orthopedic surgeons for treatment is not possible. However, a proper, blindly and independently conducted judgment of the X-rays in both trial groups is essential for the primary outcome. Two orthopedic surgeons will judge all X-rays of the patients of both groups and calculate the Cobb angles. To ensure blinding of the primary outcome, the randomization status of the participants will not be disclosed to these two orthopedic surgeons, who judge the patient's X-rays.

### Statistical methods

The intervention and control group will be compared based on the 'intention to treat' principle. Differences in Cobb angle between the two groups and other continuous parameters will be measured using parametric or non-parametric tests (depending on skewness) for group comparisons. Categorical parameters will be compared by the Chi-square test. Logistic regression will be applied to measure the treatment effect (yes/no progression) adjusting for covariates. Since we have 4-month measurements on Cobb angles in both arms, progression in Cobb angle will be analyzed with a linear mixed effect model, where we will assume a simple compound symmetry structure. This may be particularly important for extrapolations to follow-up periods longer than 2 years after entry.

When a patient in the control group had to be braced before the end of the follow-up (because of a more than 10 degree progression of the curvature), her/his Cobb angle at the moment of commencing treatment will be considered as final outcome and will be included in the analysis.

In a second analysis, we will perform Kaplan-Meier analyses with these 'progression to more than 10 degrees' as events, in both arms (intention-to-treat).

Stratified analysis will be done to evaluate whether curve type, brace compliance, Cobb angle at inclusion and Risser sign at inclusion influence the effectiveness of brace treatment. Using logistic regression we will also evaluate whether brace compliance depends on gender and age.

Health-related quality of life and utilities will be compared between the intervention and control group. This will be done by basic descriptive statistics. Depending on the distribution of the data, parametric or non-parametric tests will be used.

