### Outcomes

The primary outcome of this RCT is that bracing will be considered potentially effective, if after two years the mean progression of the abnormal curvature in the intervention group is at least 5 degrees less than in the control group. Two years after date of randomization the primary outcome measure, progression in Cobb angle, will be established in each patient. Mean Cobb angles, as reported independently, in the intervention arm will be compared to mean Cobb angles in the control arm. To reduce inter-observer measurement errors, two orthopedic surgeons associated with the project team will judge all X-rays independently and without knowledge of the allocation arm. The mean value of the observed Cobb angles will serve as assessed value, whenever the difference between the two measurements is less than 3 degrees. If the difference is larger, a third orthopedic surgeon will be asked to measure the Cobb angle; the mean Cobb angle of all 3 measurements will serve as the assessed value.

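### The Cobb-angle comparison may switch to a rank test on observed skewness although the criterion is a 5-degree difference in mean progression, and no single primary analysis is fixed

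*Protocol article*

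**What the plan says.** **The question.** Objectives and Outcomes judge bracing by whether mean progression over two years is at least 5 degrees less than in the control group. Sample size uses the same quantity: "a mean difference of 5 degrees between the groups can be detected with 40 patients in both study arms", with a standard deviation of change of about 4.5 degrees.

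**The comparison.** Outcomes names progression in Cobb angle as the primary outcome measure, then continues: "Mean Cobb angles, as reported independently, in the intervention arm will be compared to mean Cobb angles in the control arm". The Abstract likewise lists the two-year Cobb angle as a main outcome.

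**The analysis.** Statistical methods states: "Differences in Cobb angle between the two groups and other continuous parameters will be measured using parametric or non-parametric tests (depending on skewness"). It gives no threshold for skewness. The same section adds a linear mixed model of progression on the four-monthly angles, and a model for a binary outcome: "Logistic regression will be applied to measure the treatment effect (yes/no progression) adjusting for covariates". Baseline Cobb angle and Risser sign appear by name only in stratified analyses of whether the brace effect varies. No analysis is called primary.

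**The design.** Under Randomization: "Lists will be constructed with randomly permuted blocks per stratum, where strata will be defined by the participating center". Centre is the only stratification factor, and no analysis named in Statistical methods includes it.

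**The concern.** Three things do not fit together.

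1. The success criterion is a number of degrees on the mean scale. If the data look skewed, the stated rule replaces the comparison of means with one of ranks, whose p-value cannot be read against 5 degrees. The target of the analysis would then depend on the outcome data.
2. Progression and final angle are different variables with different variances. Outcomes uses both, and the mixed model is a third route to the same question. With no primary analysis named, the trial could report several answers.
3. Baseline Cobb angle and centre are known for every patient, but no analysis of the continuous outcome is stated to adjust for them. The one analysis stated to adjust for covariates first reduces the angle to yes or no.

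At stake are a conclusion that may not answer the question posed, and some avoidable loss of precision.

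**Working it through.** **Inputs from the protocol.** Difference 5 degrees; SD of change 4.5; power 95%; alpha 0.05 (taken as two-sided); 40 per arm; Cobb angle at inclusion 22 to 35 degrees; change at two years 0 to 15 degrees, assumed uniform.

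**Assumptions, not in the protocol.** Baseline uniform on 22 to 35; correlation r between baseline and change of 0, varied from -0.3 to 0.5; intraclass correlation for centre 0.05 to 0.20; the distribution shapes in step 3.

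**Step 1. The plan's own figure.** n per arm = 2(1.960 + 1.645)² × 4.5² / 5² = 21.05, so 22 (23 with the t distribution), not 40. At 40 per arm the SE is 4.5 × √(2/40) = 1.006 and power is Φ(5/1.006 − 1.96) = 99.9%. The mismatch with 40 is a separate matter. Here it shows that power is ample if change is compared.

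**Step 2. Final angle against change.**
- Baseline SD = 13/√12 = 3.75.
- Final-angle SD at r = 0: √(3.75² + 4.5²) = 5.86. Variance ratio (5.86/4.5)² = 1.70.
- SE at 40 per arm: 5.86 × √(2/40) = 1.31, against 1.006 for change.
- 95% CI half-width: 1.96 × 1.31 = 2.6 degrees, against 1.96 × 1.006 = 2.0.
- Power for 5 degrees with final angles: Φ(5/1.31 − 1.96) = 97%.

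For other r, final-angle SD = √(3.75² + 4.5² + 2r × 3.75 × 4.5) and ANCOVA SD = 4.5 × √(1 − r²):

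| r | SD, final angle | Power, final angle | SD, change | Power, change | SD, ANCOVA |
|---|---|---|---|---|---|
| -0.3 | 4.92 | 99.5% | 4.5 | 99.9% | 4.29 |
| 0 | 5.86 | 96.8% | 4.5 | 99.9% | 4.50 |
| 0.3 | 6.67 | 91.8% | 4.5 | 99.9% | 4.29 |
| 0.5 | 7.16 | 87.8% | 4.5 | 99.9% | 3.90 |

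ANCOVA is never less precise than either unadjusted comparison, apart from the degree of freedom spent. Its gain over change is small or nil, and its gain over final angles is larger.

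**Step 3. The skewness rule.** 10,000 simulated trials, 40 per arm. The rule uses Mann-Whitney if a skewness test is significant at 5% in either arm, and the Welch t-test otherwise. Means are equal throughout, so a rejection is a false signal of a mean difference.

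| Arms | t-test | Rank test | Skewness rule |
|---|---|---|---|
| Both uniform 0-15 | 5.0% | 4.7% | 5.0% |
| Both gamma (skewed) | 4.8% | 5.1% | 5.2% |
| Uniform v 80/20 mixture | 4.9% | 6.2% | 6.5% |
| Normal v 80/20 mixture | 5.0% | 9.0% | 9.8% |
| Uniform v exponential | 5.7% | 18.2% | 18.3% |

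The rule holds its level when the shapes agree. When they differ, the rank test can reject with no mean difference at all.

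Unequal shapes are plausible here. A control patient braced after more than 10 degrees of progression has the angle at that moment taken as final, and no such rule is stated for the brace arm. With control change uniform on 0-15, values above 10 recorded at 10-12, and equal means, the rank test rejected in 8.0% of runs against a gamma brace arm with SD 4.5 and in 21.6% against an exponential one (Welch t-test 5.4% and 6.0%). Against a uniform brace arm there was no excess (5.3%).

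**Step 4. Centre.** Stratification balances centre between arms, so the true SE is smaller by a factor √(1 − ICC) than an unadjusted test assumes. The actual level of a nominal 5% test is 2[1 − Φ(1.96/√(1 − ICC))]: 4.4% at ICC 0.05, 3.9% at 0.10 and 2.8% at 0.20. Adjusting lowers the 22 per arm of step 1 to 20, 19 and 17. Leaving centre out is therefore conservative.

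**The case against.** **The two-sample test is not the stated primary analysis.** A reader might infer that it is. Statistical methods does not say so, and it also plans a mixed model of progression, the very quantity that Outcomes calls the primary outcome measure. This stands. The defect is that the primary analysis is not fixed, not that a wrong one was chosen.

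**Baseline is not ignored if progression is compared.** Change already subtracts it, and most of the document speaks of change. The final-angle reading rests on one sentence of Outcomes and on the Abstract. This stands too: the 1.7 ratio is conditional on that reading, and even then power is about 97% at r = 0.

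**Chance imbalance and strata.** A reader might count chance baseline imbalance as a further harm. Under randomisation it is imprecision, already contained in the SE of 1.31. A reader might also take the omission of centre to inflate false positives; step 4 shows the opposite. Risser sign is not a randomisation stratum, so omitting it costs at most some precision.

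**Detail may sit elsewhere.** The article condenses a fuller plan. Covariate lists, the handling of centre and a skewness threshold are commonly given there, so their absence alone is no error. This stands for those items.

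**The rank-test problem is conditional.** The protocol assumes a uniform, hence symmetric, change. Under a pure shift a rank test is also valid for the mean shift, and a rank p-value does not prevent reporting the mean difference. That limits the size of the problem. It does not remove a stated rule that lets the observed data decide whether the test addresses the stated criterion.

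**Conclusion.** The point holds in a limited form. The stated rule can replace the mean comparison with a rank test that does not address the 5-degree criterion, progression and final angle are used interchangeably, and no analysis is named primary. These are features of what the text says, not of what it leaves out.

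The size is moderate and depends on assumptions. False signals of a mean difference reached 9% to 18% for two assumed pairs of shapes and 6% for a third, with none in excess when shapes agreed. Comparing unadjusted final angles costs a variance factor of about 1.7 at r = 0. Power falls below the planned 95% only if baseline and change are positively correlated to some degree (91.8% at 0.3, 87.8% at 0.5). If change is compared, power is about 99.9% on the protocol's inputs and adjustment adds little. The documents do not support a claim of bias or of inflated error from omitting baseline, Risser sign or centre.

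**What to change.** Name one primary analysis: an ANCOVA of the two-year Cobb angle, or the month-24 contrast of the mixed model, adjusted for baseline Cobb angle and centre (as a random effect, or with small centres pooled). Risser sign may be added as an optional covariate for precision.

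Report the adjusted mean difference with its 95% CI whatever the skewness, with robust or bootstrap standard errors if needed, and read it against the 5-degree criterion. Keep rank tests and the yes/no logistic model as supportive.

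In Outcomes, say in one wording what is compared. With baseline in the model, the treatment effect is the same whether the response is the final angle or the change.

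The cost is a change of wording and a few degrees of freedom for centre. Baseline Cobb angle and Risser sign are already recorded at inclusion, and centre is known from randomisation.

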**Methods:**

A randomized controlled trial was designed. Eligible patients are girls and boys in the age group 8–15 years whose diagnosis of IS has been established by an orthopedic surgeon, who have not yet been treated by bracing or surgery, and for whom further growth of physical height is still expected based on medical examination and maturation characteristics (Risser ≤ 2). The Cobb angle of the eligible patient should either be minimally 22 and maximally 29 degrees with established progression of more than 5 degrees, or should be minimally 30 and maximally 35 degrees; established progression for the latter is not necessary. A total of 100 patients will be included in this trial. The intervention group will be treated with full-time Boston brace wear; the control group will not be braced. Every four months, each patient will have a physical and an X-ray examination. The main outcomes will be the Cobb angle two years after inclusion and health-related quality of life.

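### The trial asks about mean two-year progression, but the abstract, Outcomes and Statistical methods drift to the Cobb angle itself and do not tie the 5-degree rule to one analysis

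*Protocol article*

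**What the plan says.** All places are in the protocol article.

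- **Objectives** (research question 1) and the **abstract's** statement of aim ask whether mean progression after two years is at least 5 degrees less with bracing.
- **Outcomes** turns this into a rule for judging the brace. The condition is: "if after two years the mean progression of the abnormal curvature in the intervention group is at least 5 degrees less than in the control" arm. It adds: "Two years after date of randomization the primary outcome measure, progression in Cobb angle, will be established in each patient".
- The next sentence of **Outcomes** changes the variable: "Mean Cobb angles, as reported independently, in the intervention arm will be compared to mean Cobb angles in the control arm". That is a level, not a change.
- The **abstract** (Methods) also uses the level, and puts quality of life beside it: "The main outcomes will be the Cobb angle two years after inclusion and health-related quality of life". Outcomes lists quality of life as secondary.
- **Sample size** gives alpha once, 0.05, for a 5-degree mean difference with 40 per arm. It takes the SD of change as about 4.5 degrees, from a uniform spread of 0 to 15.
- **Statistical methods** lists three analyses without ranking them. The group test: "Differences in Cobb angle between the two groups and other continuous parameters will be measured using parametric or non-parametric tests". The logistic model: "Logistic regression will be applied to measure the treatment effect (yes/no progression) adjusting for covariates". The repeated-measures model: "progression in Cobb angle will be analyzed with a linear mixed effect model". Only the Kaplan-Meier analysis is explicitly placed second.

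**The concern.** Read literally, the measure that Outcomes calls primary (progression) is assigned to the mixed model. The group test, which is what the sample size fits, is assigned to a different variable (Cobb angle). A third model, on a yes/no outcome with no stated cut-off, is also said to estimate the treatment effect. The section does not say which estimate is held against 5 degrees, and an odds ratio cannot be held against it at all.

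Two things are at stake. If the reported result can be picked from several analyses, the false-positive rate exceeds the single stated 0.05. If the comparison is made on the final angle instead of change, the trial loses precision, because the spread of baseline angles enters the comparison.

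**Working it through.** **The plan's own figure.** n per arm = 2(z₀.₉₇₅ + z₀.₉₅)² SD² / δ² = 2(1.960 + 1.645)² × 4.5² / 5² = 21.05, so 22 per arm (two-sided; the document does not state sidedness). The stated 40 is not reproduced. It fits an SD near 6.2; for example 15/√12 × √2 = 6.12 gives 39. The planned number is therefore generous for the stated SD. That is a separate matter, but it explains the high power at 5 degrees below.

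**Inputs from the document.** 40 per arm; two-year change uniform over 0 to 15; baseline range 22 to 35; a visit every four months (7 readings including baseline).

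**Inputs assumed.** Baseline uniform over its range; linear course; reading error SD 1 degree (about the stated maximum of 2 degrees at 95%); yes/no progression cut at 5 degrees; bracing of controls not modelled.

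**Change against final angle, in closed form.**
- SD of change = √(15²/12 + 1² + 1²) = √20.75 = 4.56, in line with the plan's 4.5.
- SD of final angle = √(15²/12 + 13²/12 + 1²) = √33.83 = 5.82.
- SE of a difference between arms = SD × √(2/40), giving 1.02 and 1.30.
- Power ≈ Φ(δ/SE − 1.96):

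| True difference | Change | Final angle |
|---|---|---|
| 2.5 degrees | Φ(0.49) = 69% | Φ(−0.04) = 48% |
| 5 degrees | Φ(2.95) = 99.8% | Φ(1.88) = 97% |

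The two estimates differ by the chance imbalance in measured baseline. Its SE is √(13²/12 + 1²) × √(2/40) = 3.88 × 0.224 = 0.87, so they can lie up to about 1.96 × 0.87 = 1.7 degrees apart. That is a third of the 5-degree threshold.

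Reading error matters somewhat. In simulation at a true 3 degrees, power is 83% (error SD 1) or 73% (SD 2) for change, against 62% and 59% for final angle.

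**Picking among analyses with no true effect** (6,000 simulated trials, 40 per arm, each test at 0.05):

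| Any of these significant | False positives |
|---|---|
| Change or slope | 5.8% |
| Change, logistic or slope | 8.4% |
| The same plus final angle | 11.1% |

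Monte Carlo error is about 1.96 × √(0.084 × 0.916/6000) = 0.7 percentage points. Three independent tests would give 1 − 0.95³ = 14.3%; the lower figures reflect strong correlation. The slope analysis used here is a t-test on per-patient slopes with correct size, so these figures do not depend on the compound-symmetry assumption.

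**Disagreement on significance among change, logistic and slope.** At a true 2.5 degrees it is about 40% of trials. At 5 degrees it is 12.5% with a 5-degree cut-off for progression, and 3.4% with a 10-degree cut-off, the only progression threshold that Statistical methods gives.

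**The case against.** The strongest reply is that the document does state its deciding contrast. The abstract's aim, research question 1, the Outcomes rule and the sample size all refer to a 5-degree difference in mean two-year progression. No sentence lets an odds ratio, a slope or a survival curve establish effectiveness. This stands. A reader might infer that nothing decides the trial, or that every listed analysis is tested at a full 0.05. The text supports neither: alpha appears once, attached to the mean difference, and the other analyses are given none.

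Further points that stand:
- If the 5-degree rule is applied to the observed difference in change, false positives all but vanish: 5/1.02 is 4.9 standard errors, and none of 6,000 null trials reached it.
- Under randomization, final angle and change estimate the same treatment difference. They differ in precision, not in target.
- Adding the Kaplan-Meier comparison would raise the false-positive figure to about 13%, but that analysis is already ranked second and should not be counted.
- The mixed model has a stated purpose, in particular extrapolation beyond two years.
- Ranking labels alone could sit in an analysis plan that is not shown.

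What the reply does not remove is the conflict in the published text. Outcomes names progression and then compares angles, the abstract names the angle, and Statistical methods splits the two variables between methods. An unseen plan cannot make those sentences agree.

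**Conclusion.** The point holds as an inconsistency in the text with a moderate statistical consequence. The intended contrast can be recognised, but the document does not carry it through to one variable and one analysis. Free choice among the change, logistic and slope tests would give about 8% false positives, and about 11% with the final angle added. Most of the excess over the 5.8% for change or slope comes from the logistic model and the final angle. Using the final angle instead of change costs about 20 percentage points of power at a true 2.5 degrees and little at 5 degrees, where both exceed 96%.

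It would be too strong to say that the analyses will often contradict each other. At the design difference they disagree in about 3 to 13% of trials, and disagreement means significant against not significant, not opposite directions.

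The figures rest on the assumed linear course, uniform baseline, reading error and progression cut-off. They also omit the rule that takes a braced control's angle at the start of bracing as final. With uniform change over 0 to 15, about 5/15, or a third, of controls would pass 10 degrees, so that omission is not trivial.

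**What to change.** - **Abstract, Outcomes and Statistical methods:** state that the deciding analysis is the between-arm difference in mean change in blinded Cobb angle from inclusion to two years, tested once at 0.05, and that the 5-degree rule refers to this estimate.
- **Outcomes:** replace the comparison of mean Cobb angles with a comparison of mean progression.
- **Abstract:** give progression as the primary outcome, and list quality of life as secondary, as Outcomes does.
- **Statistical methods:** state that the logistic, mixed-model and Kaplan-Meier results are supportive.

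The cost is wording only: no added patients, visits or measurements. The sponsor gives up claiming effectiveness from a supportive analysis.

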### Participants

Eligible patients are girls and boys in the age group 8–15 years whose diagnosis of IS has been established by an orthopedic surgeon, who have not yet been treated by bracing or surgery, and for whom further growth of physical height is still expected based on medical examination and maturation characteristics (Risser sign) established by X-ray. To expect further growth of physical height, only patients with a Risser sign ≤ 2 will be included. All participating orthopedic surgeons agreed that the Cobb angle of the eligible patient should either be minimally 22 and maximally 29 degrees with established progression of more than 5 degrees, or should be minimally 30 and maximally 35 degrees; established progression for the latter is not necessary. At inclusion of the study, data on calendar age, gender, height, maturation characteristics (Risser sign, menarche), size and location of the curvature will be recorded for all patients.

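### The only treatment effect that the plan states to be covariate-adjusted is an odds ratio for yes/no progression; estimating it in degrees would match the 5-degree criterion and lose less information.

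*Protocol article*

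**What the plan says.** The Outcomes section of the protocol article puts the primary outcome on a continuous scale: "Two years after date of randomization the primary outcome measure, progression in Cobb angle, will be established in each patient". The success criterion is stated as a mean difference: "if after two years the mean progression of the abnormal curvature in the intervention group is at least 5 degrees less than in the control" arm. Research question 1 under Objectives is framed the same way.

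The Statistical methods section lists several analyses:

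- A two-group comparison: "Differences in Cobb angle between the two groups and other continuous parameters will be measured using parametric or non-parametric tests". Covariates are not mentioned.
- A logistic model: "Logistic regression will be applied to measure the treatment effect (yes/no progression) adjusting for covariates". Among the treatment-effect analyses, only this sentence mentions covariates.
- A longitudinal model: "progression in Cobb angle will be analyzed with a linear mixed effect model, where we will assume a simple compound symmetry structure". Covariates are neither named nor excluded. The stated motives are the four-monthly measurements and extrapolation beyond two years.
- A time-to-event analysis: "we will perform Kaplan-Meier analyses with these 'progression to more than 10 degrees' as events".
- Stratified analyses by curve type, compliance, inclusion Cobb angle and Risser sign. These ask whether the effect varies and do not give an adjusted overall effect.

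The section also says that a control who is braced early, after more than 10 degrees of progression, keeps the angle at brace start as the final outcome.

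**The concern.** The scale of the adjusted estimate does not match the scale of the question. The effect is sought in degrees and judged against 5 degrees, but the one effect said to be adjusted is an odds ratio for a yes/no version of the same measurement. That has two consequences.

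- The adjusted result cannot show whether the 5-degree criterion still holds once baseline covariates are taken into account. Its size also depends on where the cut falls.
- Any cut treats patients on the same side of it as equal, so the adjusted analysis is less sensitive than the data allow. It could disagree with the main comparison because of the cut alone.

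**Working it through.** **Inputs from the Sample size section.** True difference 5 degrees, SD of change about 4.5, alpha 0.05, power 95%, 40 per arm. For the spread of change: "After two years, when the outcome will be determined, the range in change will be 0–15 ± 2 degrees", taken as uniform. Two numeric meanings of progression appear elsewhere: the entry rule ("minimally 22 and maximally 29 degrees with established progression of more than 5 degrees") and the event of more than 10 degrees.

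**Assumptions of mine.** Reading-error SD of 1 degree per film (the stated maximum of 2 degrees read as about two SDs), bracing shifts every change by the same amount, two-sided testing.

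**The plan's own figures.**
- SD: a uniform 0–15 change has SD 15/√12 = 4.33. Adding two independent reading errors gives √(4.33² + 1² + 1²) = √20.75 = 4.56, in line with the stated 4.5.
- Sample size: 2 × (1.960 + 1.645)² × 4.5² / 5² = 21.05, so 22 per arm. The stated 40 is not reproduced; it would need an SD of about 6.2. The difference is on the safe side and is separate from this point.

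**Power in degrees, 40 per arm.** The standard error is 4.56 × √(2/40) = 1.02.
- True 3 degrees: 3/1.02 − 1.96 = 0.98, power about 84% by the normal approximation and 83% by simulated t-test.
- True 5 degrees: 5/1.02 − 1.96 = 2.94, power 99.8%.

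**Power after a cut.** Simulation of 20,000 trials per setting: control change uniform on 0–15, brace change the same minus the true difference, reading error added to both, uncorrected chi-square test on the share above the cut.

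| True difference | Cut | Control v brace above cut | Power, yes/no | Power, degrees |
|---|---|---|---|---|
| 3 | >5 | 67% v 47% | 46% | 83% |
| 3 | >10 | 33% v 14% | 56% | 83% |
| 5 | >5 | 67% v 33% | 88% | 99.8% |
| 5 | >10 | 33% v 4% | 97% | 99.8% |

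**Dependence on the cut.** For the same true 5 degrees, the unadjusted odds ratio is (0.667/0.333)/(0.333/0.667) = 4.0 at the cut of more than 5. At more than 10 it is (0.333/0.667)/(0.038/0.962), about 13.

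**With the rule for controls braced early.** Suppose every control above 10 degrees is braced and held at 10.75. A true 3 degrees then appears as about 2.35, and power in degrees falls to about 70%. Yes/no power at more than 10 stays at 56%, because those controls are still events. A true 5 degrees appears as about 4.4.

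**Check with a different shape.** Take normal change with SD 4.5, an assumed control mean of 7.5 (the middle of 0–15) and a brace mean of 2.5.
- Cut at more than 5: shares Φ(2.5/4.5) = 71% v 29%; 34 per arm for 95% power; power 97.7% at 40 per arm.
- Cut at more than 10: 29% v 5%; 60 per arm; power 83.6%.
- In degrees: 22 per arm; power 99.9%.

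For normal data even a median split keeps at most 2/π = 64% of the information. Which cut does better depends on the shape, but both do worse than degrees under either one.

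**The case against.** The best defence is that the logistic model is an addition. Research question 1 is answered by the group comparison in degrees, the mixed model is also in degrees and could carry covariates, and nothing asks the odds ratio to match a mean difference. At the 5-degree design effect, yes/no power is still 88% to 97%; the large gaps appear at 3 degrees, below the trial's own criterion. The power figures compare unadjusted tests, not the adjusted models themselves. The rule for controls braced early also takes away part of the advantage of degrees, and the fix does not remove that effect.

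All of this stands and limits the point. It does not remove it: the only adjustment actually stated is still on the cut scale, and degrees keep an advantage under the early-bracing rule.

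A reader might infer three stronger things, which the article does not support.

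- *Half of all stable curves would count as progressed.* That needs a cut at zero, where symmetric reading error gives 50%. The article never sets that cut; where it puts a figure on progression in its entry, bracing and Kaplan–Meier rules, the figure is more than 5 or more than 10 degrees. At a cut of 5 the rate is about 0.02% with the assumed reading error, and about 8% only if the unreduced 5-degree error is taken as the 95% limit for each reading.
- *The absent cut or confirming film is itself an error.* A condensed article may leave such detail to the full protocol or analysis plan.
- *The primary test is weakened, or logistic regression is the only adjusted analysis allowed.* The article says neither.

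**Conclusion.** The point holds as a cheap improvement. The one treatment effect stated to be covariate-adjusted dichotomises the continuous primary outcome, gives a result that cannot be judged against 5 degrees, and loses power at either cut for which the article supplies a figure.

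The loss is modest at the design effect (99.8% down to 88% or 97%) and substantial at 3 degrees (83% down to 46% or 56%). At 3 degrees it is about 70% against 56% for the cut at more than 10 if all controls past 10 degrees are braced and held near 10.75. These sizes rest on the uniform 0–15 change from the article and on the assumed reading-error SD, parallel shift and unadjusted tests; a normal shape changes the figures but not the direction. The primary comparison and the mixed model are not affected.

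**What to change.** In Statistical methods, state that the covariate-adjusted treatment effect will be estimated in degrees. Either of two routes will do: linear regression of two-year progression on arm and the same covariates, including Cobb angle at inclusion, or those covariates added to the planned linear mixed model. Report the logistic analysis as supportive, with the event of more than 10 degrees already defined for the Kaplan–Meier analysis.

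The cost is about a sentence of analysis wording and no new data. The small downside is that the odds ratio becomes supportive only. The handling of angles recorded at brace start is a separate matter, which this change leaves as it is.
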